**Methods:**

The HOSENG (HOme-based SElf-testiNG) trial is a cluster-randomized, parallel-group, superiority trial in two districts of Lesotho, Southern Africa. Clusters are stratified by district, village size, and village access to the nearest health facility. Cluster eligibility criteria include: village is in catchment area of one of the study facilities, village authority provides consent, and village has a registered, capable, and consenting village health worker (VHW). In intervention clusters, HIV self-tests are provided for eligible household members who are absent or decline HIV-testing in the presence of the campaign team. In control clusters, standard of care for absent and refusing individuals applies, i.e., referral to a health facility. The primary outcome is HIV-testing coverage among individuals aged 12 years or older within 120 days after enrollment. Secondary objectives include HIV-testing coverage among other age groups, and uptake of the different testing modalities. Statistical analyses will be conducted and reported in line with CONSORT guidelines. The HOSENG trial is linked to the VIBRA (Village-Based Refill of ART) trial. Together, they constitute the GET ON (GETting tOwards Ninety) research project.

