## Background

The United Nations Programme on HIV/AIDS (UNAIDS) has shown a way forward in controlling and finally ending the deadly acquired immune deficiency syndrome (AIDS) epidemic by launching the 90-90-90 strategy [1]. The first target is to ensure that 90% of all people living with human immune deficiency virus (HIV) are aware of their status. The second target is that 90% of those diagnosed receive sustained antiretroviral therapy (ART). And the third target stands for 90% of those receiving ART achieving viral suppression. Globally, in 2017, progress towards the first UNAIDS target, i.e., that 90% of people living with HIV are aware of their status, was lower than other stages of the HIV care cascade [2]. The most recent data from Eastern and Southern Africa show that the percentage of people living with HIV who know their HIV status has steadily improved in the last few years, currently at a level of 81% (64–95%), but still leaving a gap of approximately 1.7 million HIV-positive people to reach the target of 90% knowing their HIV status [3, 4]. In order to reach the first UNAIDS target, home-/community-based testing, i.e., HIV-testing close to where people live or work, is a key strategy endorsed by the World Health Organization (WHO) [5, 6]. Many studies from Southern Africa, including Lesotho, have shown that home-based HIV-testing is highly promising for closing the crucial gap to achieve the first 90 [7]. Yet, it is critical to distinguish between the principal acceptance (uptake) of HIV-testing and the HIV-testing coverage. While in most cases the former is above 90%, the coverage often remains below 90% due to the household members who are absent at the time of the campaign, mainly men and young adults [8].

HIV self-testing (HIVST) has proved to be an accurate diagnostic tool that increases uptake of HIV-testing, facilitates linkage to care among target populations, and may be more cost-effective than provider-delivered HIV-testing [9–17]. Thus, WHO strongly endorses oral HIVST [18]. In a WHO review, 16 countries reported having a policy supportive of HIVST, including Lesotho [19, 20].

However, to date only limited data are available, assessing the effect of oral HIVST in increasing HIV-testing coverage. This randomized controlled trial thus aims to determine the added effect of distributing oral HIVST to individuals absent or refusing to test during a home-based HIV-testing campaign on HIV-testing coverage.

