## Methods

### Setting

The HOSENG (HOme-based SElf-testiNG) trial will be conducted in the districts of Butha-Buthe and Mokhotlong, in Northern Lesotho, Southern Africa, in the catchment areas of 22 health facilities. Both districts are characterized by mostly rural settings with an estimated population of 220,000, mainly subsistence farmers and mine workers as well as construction or domestic laborers who work in neighboring South Africa. Each district has only one mid-size town: Butha-Buthe with approximately 25,000 inhabitants, and Mokhotlong with approximately 10,000 inhabitants. The remaining population lives in villages scattered over a mountainous area of 5842 km^2^. According to the recent household-based national survey from 2016 to 2017 the adult HIV prevalence is 17.8% in Butha-Buthe and 26.1% in Mokhotlong [21].

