### Procedure

Two to three specifically trained teams, each consisting of five to six lay-counselors, one campaign organizer and one supervising study nurse will visit all households in selected villages, going from door to door. The teams will propose HTC and multi-disease screenings and prevention. The population of the selected areas are informed about the campaign beforehand by their village chief. Specifically, the campaign team will arrive in the village in the morning, meet with the village chief and then start systematically visiting all households in the pre-defined area by going from door to door. At the household, the teams will proceed as follows:The counselor will introduce him- or herself and explain the purpose of the testing/screening campaignThe counselor will ask the head of household or their representative (aged 18 years and older) for written informed consent to the testing/screening campaign, and to obtaining data about present and absent household members for study purposeIf the head of household or the representative refuses their household participation, the team will leave the house, record the refusal reason, and proceed to the next householdThe counselor will assess the total number of present and absent household membersDefinition of household member: (1) is acknowledged by the household head or the representative as part of the household and (2) sleeps in the household regularly (at least once a month), and (3) if absent during the campaign: returns to the household no later than 3 months after the date of the home visitThe counselor will provide information about HIV and testing, prevention aspects, and the other disease screenings (see below)The counselor will assess the HIV status of all household members and screen the patient’s health booklets (“*bukana*”)Household members who are eligible for and consent to testing (by filling in the Lesotho national informed consent form for HIV-testing) undergo HIV-testing by the counselor according to specific cluster-arm allocation procedure and according to national HIV-testing guidelines [20]. For absent or declining household members the specific procedures differ between the two cluster arms and are described in detail below in the section on intervention clusters. Figure 2 presents all possible HIV-testing scenarios during the campaignOnce the HIV test is done, the counselor documents the result in the patient’s health booklet and provides post-test counseling. If the HIV test is confirmed positive, the counselor contacts the study nurse, who then provides further counseling and assesses the participant for enrollment into the inter-linked follow-up study (VIBRA trial [22])

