#### Intervention clusters

Figure 4 summarizes the procedures in the HOSENG clusters and Fig. 5 the Standard Protocol Items: Recommendations for Interventional Trials (SPIRIT) flow diagram. In the intervention clusters, the campaign team will leave an oral HIVST kit (OraQuick® ADVANCE HIV I/II, second generation serology assay with a sensitivity of > 93%, a specificity of > 99 [27–30]) for every household member aged 12 years or older who is absent or declined HIV-testing on the day of the campaign. We chose 12 years as the threshold because adolescents are an important risk group and this is the legal age for providing HIV-testing consent in Lesotho [24]. The household can refuse to have an oral HIVST left behind for their absent household members. The oral HIVST kit is prepacked, includes a written and pictoral instruction for use in the local language, Sesotho, and the package is labelled with a written request to consult the VHW within 2 weeks after use of the test – irrespective of the result. In cases where more than one trained VHW serves the village, the household will be asked for the VHW of choice. The team will label the kit with the name of the absent member before dispensation.

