**Fig. 5 Fig5:**
[figure not shown]
Standard Protocol Items; Recommendations for Interventional Trials (SPIRIT) flow diagram of the HOme-based SElftestiNG (HOSENG) trial

One household member – the one with the closest relation to the absent person(s) – will be tested and trained using the oral HIVST. All other present household members will be tested using the standard blood-based point-of-care HIV test according to Lesotho national guidelines [20].

The VHWs in the intervention custers will receive a list of all household members for whom an oral HIVST was dispensed. The VHW will visit all households 2–4 weeks after the campaign to collect the oral HIVST in case the oral HIVST is not returned to the VHW. If an oral HIVST is reactive, the VHW will either provide further blood-based testing on the spot or organize referral to the nearby health facility for confirmatory testing. All VHWs from intervention clusters will receive a second extensive training session about oral HIVST, handling disclosure and stigma, and data entering on paper-based study forms and the patient’s health booklet.

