#### Control clusters

Following standard of care during home-based HIV-testing, every absent household member or those declining HIV-testing will be encouraged to get an HIV test done by the VHW or the nearby health facility. The research team will screen the registers at the health facilities in order to assess if these individuals came for testing in the timeframe of the primary endpoint window.

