### Endpoints

The primary endpoint is HIV-testing coverage among individuals aged 12 years or older in the surveyed area within 120 days after the home visit, defined as the proportion of all individuals aged 12 years or older living in a household of the surveyed area with a confirmed HIV test result.

We define a confirmed HIV-negative result as either being tested HIV-negative as per the algorithm defined in Fig. 2, or being tested HIV-negative within the last 4 weeks with proof of documentation (i.e., documentation in patient’s health booklets). We define a confirmed HIV-positive result as (1) tested HIV-positive as per the algorithm defined in Fig. 2, or (2) being tested HIV-positive but not yet on ART with proof of documentation, or (3) being on ART with proof of documentation.

The rationale for the time point of 120 days is that we leave oral HIVST kits at the households for all absent household members aged 12 years or older who return within a maximum of 3 months (see definition of household member above in the “Procedure” section). An interval of 120 days after home visit allows sufficient time for absent members to return to their households, conduct self-testing, and be followed up by the VHW.

The secondary endpoints are outlined in Table 2.

**Table 2 Tab2:** Secondary endpoints of the HOme-based SElftestiNG (HOSENG) trial

	Endpoint	Definition	Time point following enrollment
1	Testing coverage irrespective of age	Proportion of all individuals living in a household of the surveyed area with a confirmed HIV test result	Within 120 days
2	Blood-based HIV-testing uptake	Proportion of all present individuals living in a household of the surveyed area, being eligible for blood-based HIV-testing and accepting to be tested using blood-based point-of-care HIV test	On the day of the campaign
3	Oral-based HIV-testing uptake	Proportion of all individuals living in a household of the surveyed area for whom an oral HIV self-test (HIVST) was left behind and who performed it	Within 120 days

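### The 120-day primary endpoint is ascertained by different follow-up routes in the two arms, and one common register search would largely remove the difference

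*Protocol article*

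**What the plan says.** **Definition.** Under Endpoints, a positive status counts if it is established through the trial's testing algorithm (Fig. 2), if an earlier positive result in a person not yet on ART is documented, or by "being on ART with proof of documentation". The window is 120 days from the home visit.

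**At the visit, both arms.** Under Procedure, "The counselor will assess the HIV status of all household members", and health booklets are screened. Nothing here differs by arm.

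**After the visit, intervention.** A kit is left "for every household member aged 12 years or older who is absent or declined HIV-testing on the day of the campaign" (Intervention clusters). Endpoints again speaks of all absent members from age 12. The VHW holds a list of the people for whom kits were left and visits at 2–4 weeks to collect kits not yet returned. "If an oral HIVST is reactive, the VHW will either provide further blood-based testing on the spot or organize referral" for confirmation at a facility. Data collection and management describes VHW paper forms for following up dispensed kits. A household may refuse the kit.

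**After the visit, control.** Absent or declining members are encouraged to test with the VHW or at the facility. The follow-up described is this: "The research team will screen the registers at the health facilities in order to assess if these individuals came for testing", within the endpoint window.

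The register check appears only under Control clusters. Its stated purpose is testing, not ART or an earlier diagnosis.

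**The concern.** The endpoint is a proportion of people with a confirmed result, so anyone whose result exists but is not looked for is scored as not covered. If the arms look in different places, part of the coverage difference reflects the looking.

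Two groups are exposed:

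- **Known positives without proof at the visit.** Someone on ART has little reason to come for testing, so a check for testing is poorly suited to finding them in control clusters. In intervention clusters the same person can be confirmed by re-testing.
- **Intervention members who bypass the kit.** Someone who tests at a facility, or whose household refused the kit, is found only through a facility record. That look-up is described for control only.

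Adjusting for HIV-testing history, as planned under Analyses, does not repair an outcome that is itself recorded differently. The planned cost per additional confirmed result would carry the same error.

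**Working it through.** **1. The plan's own figure.** Sample size gives 386 people without clustering for 63% versus 78%, 90% power, two-sided 5%. With the pooled normal approximation, mean proportion 0.705:

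n per arm = [1.960 × √(2 × 0.705 × 0.295) + 1.282 × √(0.63 × 0.37 + 0.78 × 0.22)]² / 0.15² = 192.2, rounded up to 193; total 386. It reproduces. About 10,000 people are expected and the largest requirement in Table 3 is 3,204, so power is not the issue.

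**2. Known positives: size of the group.**

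- Absent share. Background says of acceptance and coverage: "While in most cases the former is above 90%, the coverage often remains below 90% due to the household members who are absent". Taking acceptance among those present as 90–100% and coverage as 63%: 1 − 0.63/0.90 = 30.0%; 1 − 0.63/1.00 = 37.0%.
- Adult prevalence 17.8–26.1% (Setting); awareness of status 81% (Background, regional).
- Absent and already aware: 0.30 × 0.178 × 0.81 = 4.33%; 0.37 × 0.261 × 0.81 = 7.82% of the denominator.

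**3. Known positives: possible shift.** Three inputs are assumptions with no source in the document: 25–75% lack proof at the visit; 20–40.5% complete kit and confirmation (40.5% = 15/37, the average conversion that the planned effect needs); the control check finds 0–10%.

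| Case | Calculation | Points |
|---|---|---|
| Low | 4.33 × 0.25 × (0.20 − 0.10) | 0.11 |
| Midpoints | 33.5 × 0.22 × 0.81 × 0.50 × (0.30 − 0.05) | 0.75 |
| High, control finds 10% | 7.82 × 0.75 × (0.405 − 0.10) | 1.79 |
| High, control finds none | 7.82 × 0.75 × 0.405 | 2.38 |

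The midpoint is 0.75/15 = 5% of the target difference. The planned odds ratio is (0.78/0.22)/(0.63/0.37) = 2.08; at 77.25% it is 1.99.

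**4. Scale.** With 100 people per cluster and ICC 0.028, the design effect is 1 + 99 × 0.028 = 3.77. Effective size per arm is 5,000/3.77 = 1,326. The standard error of the difference is √[(0.63 × 0.37 + 0.78 × 0.22)/1,326] = 1.75 points, so the midpoint shift is 0.75/1.75 = 0.43 standard errors.

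**5. The opposite route.** Under the planned effect, 100 − 78 = 22% of the intervention arm stays uncovered. Borrowing the same 0–10% as the share of these people with a facility test that nobody looks up (again an assumption), intervention coverage is understated by 22 × 0.05 = 1.1 points at the midpoint, with a range of 0 to 2.2. This has the same order as step 3 and the opposite sign.

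**The case against.** **Kits may not go to reported positives.** The Abstract says that "HIV self-tests are provided for eligible household members who are absent or decline HIV-testing in the presence of the campaign team", and under Procedure status is assessed before the testing step. The figures were not in the text available for this review. Figs. 2 and 4 may keep kits from people reported as positive. This stands as a condition: if so, the kit route for this group closes. The body text, however, says every and all, and gives only an age limit.

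**A completed kit with confirmation is a genuine event.** This stands. Kit, VHW visit and confirmatory test are the intervention, and the result satisfies the definition. The ascertainment error is narrower: people in either arm who hold proof that nobody sought.

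**An article omits operational detail.** This stands in part. Which registers are opened may be set out in the full protocol. But the article does fix a purpose for the check and places it in one arm only, and followed as written this makes recording of the primary endpoint depend on arm.

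**A stronger reading.** A reader might infer a bias in favour of the intervention, of 2.4 points or more. The documents do not support that. The 2.38 figure puts every input at its extreme, with no detection at all in control. A figure such as 6.2 points (0.37 × 0.261 × 0.95 × 0.75 × 0.90) needs 90% completion, more than twice the 40.5% average that the planned effect requires, among people with the least reason to self-test. Neither figure subtracts the opposite route.

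**Conclusion.** The point holds as a difference in ascertainment between arms, not as a demonstrated bias in one direction. As written, dispensed-kit and VHW records feed the endpoint in one arm and a facility check for testing feeds it in the other. Each arm can miss people who meet the definition: known positives without proof in control, and facility testers or kit refusers in intervention.

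The net direction and size cannot be settled from the document. The known-positive part is under 1 point at midpoint assumptions. It rests on adult prevalence and regional awareness applied to absentees, whom Background describes as mainly men and young adults, in a denominator that starts at age 12. It also rests on unsourced values for missing proof, kit completion and control detection, and on reported positives receiving kits. The claim is clearest for absent members; a present known positive may not count as declining.

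This is a cheap improvement to the estimate and no threat to the trial's ability to answer its question.

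**What to change.** Move the register check out of Control clusters and state it once for both arms. For every absent or declining member aged 12 or older without a confirmed result, search the study facilities' HIV-testing and ART registers for the 120-day window. Count documented ART or an earlier documented positive under the existing Endpoints definition. Complete the search before names are deleted from the database (Data collection and management), because it cannot be done afterwards. State also whether members reported as HIV-positive receive kits.

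The rule uses the absence of a confirmed result, not reported status, so it does not depend on a proxy report taken by staff who know the allocation. An added analysis counting all reported positives as covered is not needed, and would override the documentation requirement.

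**Cost.** One more register at facilities already being screened, and the same look-up for intervention names.

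**Limit.** The population includes "mine workers as well as construction or domestic laborers who work in neighboring South Africa", and ART taken there is missed in both arms. The difference is therefore reduced and not removed. If registers found 80% of known positives in each arm, the extreme case would fall from 2.38 to 2.38 × 0.20 = 0.48 points, and the midpoint case to 33.5 × 0.22 × 0.81 × 0.50 × 0.20 × 0.30 = 0.18 points.

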### Endpoints

The primary endpoint is HIV-testing coverage among individuals aged 12 years or older in the surveyed area within 120 days after the home visit, defined as the proportion of all individuals aged 12 years or older living in a household of the surveyed area with a confirmed HIV test result.

We define a confirmed HIV-negative result as either being tested HIV-negative as per the algorithm defined in Fig. 2, or being tested HIV-negative within the last 4 weeks with proof of documentation (i.e., documentation in patient’s health booklets). We define a confirmed HIV-positive result as (1) tested HIV-positive as per the algorithm defined in Fig. 2, or (2) being tested HIV-positive but not yet on ART with proof of documentation, or (3) being on ART with proof of documentation.

The rationale for the time point of 120 days is that we leave oral HIVST kits at the households for all absent household members aged 12 years or older who return within a maximum of 3 months (see definition of household member above in the “Procedure” section). An interval of 120 days after home visit allows sufficient time for absent members to return to their households, conduct self-testing, and be followed up by the VHW.

The secondary endpoints are outlined in Table 2.

**Table 2 Tab2:** Secondary endpoints of the HOme-based SElftestiNG (HOSENG) trial

	Endpoint	Definition	Time point following enrollment
1	Testing coverage irrespective of age	Proportion of all individuals living in a household of the surveyed area with a confirmed HIV test result	Within 120 days
2	Blood-based HIV-testing uptake	Proportion of all present individuals living in a household of the surveyed area, being eligible for blood-based HIV-testing and accepting to be tested using blood-based point-of-care HIV test	On the day of the campaign
3	Oral-based HIV-testing uptake	Proportion of all individuals living in a household of the surveyed area for whom an oral HIV self-test (HIVST) was left behind and who performed it	Within 120 days

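### Oral-test uptake (secondary endpoint 3) is counted only among people for whom a kit was left, so kit refusals drop out and the figure exceeds uptake among all who were due a kit

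*Protocol article*

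**What the plan says.** Four places in the protocol article bear on this.

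- **Who should get a kit.** The Intervention clusters section says the team leaves one "for every household member aged 12 years or older who is absent or declined HIV-testing on the day of the campaign".
- **Refusal of a kit.** The same section adds: "The household can refuse to have an oral HIVST left behind for their absent household members".
- **How uptake is counted.** In Table 2 (Endpoints), oral uptake covers individuals "for whom an oral HIV self-test (HIVST) was left behind and who performed it", within 120 days. Blood-based uptake, on the campaign day, is the "Proportion of all present individuals living in a household of the surveyed area, being eligible for blood-based HIV-testing and accepting to be tested" with the blood-based test.
- **What uptake means.** The Background states that "it is critical to distinguish between the principal acceptance (uptake) of HIV-testing and the HIV-testing coverage". The Methods part of the Abstract lists "uptake of the different testing modalities" among the secondary objectives.

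**The concern.** A person whose household turned the kit away has had no kit left, and so falls outside endpoint 3 altogether. Refusing the kit is one of the two ways in which self-testing can fail to be taken up; the other is receiving a kit and not using it. The endpoint sees only the second. Endpoint 2, by contrast, keeps people who decline the blood test in its denominator as failures. Two figures that treat refusal differently are therefore reported under the same word.

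What is at stake is how a secondary result is read. The trial concerns people who are absent or decline, and its Discussion aims to inform testing policy. A programme planner will want to know how many oral tests are performed per person who should have had a kit. Reading endpoint 3 as that quantity would give too high an answer.

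**Working it through.** The protocol states no figure for oral uptake or for kit refusal, so there is no number of its own to reproduce. The check is algebraic, with assumed inputs.

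**Inputs**
- r = share of members due a kit whose kit was refused. Not in the protocol; assumed.
- u = share of kits left that were used within 120 days. Not in the protocol; assumed.
- D = number of members due a kit.

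**Formulas**
- Kits left = D(1-r). Tests performed = uD(1-r).
- Endpoint 3 as defined = uD(1-r) / [D(1-r)] = u, whatever r is.
- Uptake among all due a kit = uD(1-r) / D = u(1-r).
- Excess = u - u(1-r) = ur. Ratio = u / [u(1-r)] = 1/(1-r).

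**Results with u = 80% assumed**

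| r | Endpoint 3 | Among all due, u(1-r) | Excess, ur | Ratio, 1/(1-r) |
|---|---|---|---|---|
| 2% | 80% | 78.4% | 1.6 points | 1.02 |
| 5% | 80% | 76.0% | 4.0 points | 1.05 |
| 10% | 80% | 72.0% | 8.0 points | 1.11 |
| 20% | 80% | 64.0% | 16.0 points | 1.25 |
| 30% | 80% | 56.0% | 24.0 points | 1.43 |

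In counts, the 20% row means that of 100 people due a kit, 20 are refused one, 80 receive one and 64 use it. Endpoint 3 is 64/80 = 80%; uptake among those due is 64/100 = 64%.

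**Wider range.** With u from 50% to 90% and r from 2% to 40%, the excess runs from 0.50 × 0.02 = 1.0 point to 0.90 × 0.40 = 36 points, and the ratio from 1/0.98 = 1.02 to 1/0.60 = 1.67. The excess is zero only if no kit is refused. In the extreme case where half the kits are refused and all the rest are used, endpoint 3 is 100% and uptake among those due is 50%.

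The identity assumes that kits left are a subset of kits due. If kits were also left for people who already had a confirmed result, both proportions should be restricted to people without one before they are compared.

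**Which other results are touched.** The primary endpoint counts everyone aged 12 or older in surveyed households, and secondary endpoint 1 everyone of any age. People whose kit was refused stay in both denominators. The cost-effectiveness analysis is tied to the primary endpoint. None of the three changes.

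**The case against.** The strongest reply is that nothing is misstated. Table 2 gives the denominator openly, and use among dispensed kits is a valid conditional proportion. That stands. The difficulty is the label: the article itself equates uptake with acceptance, and no other stated endpoint counts acceptance among all who were due a kit.

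A second reply is that endpoint 2 is conditional as well, since it covers only present and eligible people, and that an absent member whose household refused was never personally offered a test. This has some force. A proxy's refusal is not the individual's own, which is a reason to show the components separately. It does not justify leaving the refusal out of a measure called uptake.

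Third, the size is entirely assumed, and at 2% refusal it is small. That also stands; only the direction is certain.

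Two stronger readings are tempting, and the article supports neither:
- A reader might infer that the oral and blood-based figures are to be tested against each other and that this comparison is spoiled. The Analyses section announces no such contrast. A matched treatment of refusals would not make one valid, because the populations (absent or declining versus present) and the time windows (120 days versus the campaign day) would still differ.
- A reader might infer that present members who decline testing also drop out by declining the kit. The article provides for refusal only by the household and only for absent members. Refusal by a present decliner is plausible but not stated, and the point does not need it.

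**Conclusion.** The point holds in a limited form. As labelled, endpoint 3 conditions on the kit having been left, so it lies above uptake among all due a kit by a factor 1/(1-r) whenever any kit is refused. The direction follows from the definition. The size depends on r and u, which the article does not give: 1.6 to 24 points at an assumed 80% use and 2% to 30% refusal.

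It would be wrong to conclude that the trial's main result is biased or that its question goes unanswered, because the coverage endpoints and the cost-effectiveness analysis retain the people whose kit was refused. This is an inexpensive improvement to one secondary endpoint whose name promises more than its denominator delivers.

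**What to change.** 1. Define oral-based testing uptake as self-tests performed within 120 days, divided by all household members aged 12 or older in intervention clusters who were absent or declined on the campaign day and had no already confirmed HIV result under the Endpoints section. Count a refused kit as not performed. The exclusion matters: a member with documented positive status, on documented ART, or with a documented negative test in the last 4 weeks already meets the confirmed-result definition, and counting that person as a failure would understate uptake.
2. Keep the present proportion, renamed use among dispensed kits.
3. Report kits left over kits due beside it. Give all three separately for absent and for declining members, so that household refusals made on someone's behalf remain visible.

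The cost is one reworded definition in Table 2 and two added lines of reporting. The data should already exist. The Procedure section has counselors enumerate present and absent members and check HIV status and health booklets, endpoint 2 requires knowing who accepted, and village health workers receive "a list of all household members for whom an oral HIVST was dispensed". Kits not left follow by subtraction. The downside is that the stated uptake will be lower.
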